**Exploratory hypotheses**				
**1–9 and 14–16**	2 (group) × 3 (measurement)—ANOVA for repeated measures on the factor “measurement”	4	*F*-distribution	Group × measurement interaction effect
**10–12**	2 (group) × 2 (measurement)—ANOVA for repeated measures on the factor “measurement”	1	*F*-distribution	Group × measurement interaction effect
**13**	*t* test for independent samples	1	*t*-distribution	Group main effect
**14**	One-dimensional *χ*^2^ test with 2 cells	3	*χ*^2^-distribution	Group main effect

The critical, local α-errors for the 3 tests evaluating the confirmatory hypotheses are Bonferroni-adjusted to α_local_ = .05/3 = .016 to avoid exceeding a global α-error of α_global_ = .05 by performing multiple tests. For the exploratory analyses, the critical, local α-errors are not adjusted and set to a conventional level of α_local_ = .05. Owing to inflation of the global α-error by multiple testing (9 tests) to α_global_ = 1 − (1 − 0.05)^9^ = 0.37, the exploratory analyses have a descriptive character and will be used to generate future hypotheses.

Dunn’s multiple comparison procedure is used as a post hoc test because it allows hypothesis-driven and economic multiple testing. This procedure results in a minimum significant difference (ψ). The test value is t-distributed. As effect sizes, partial η^2^ and ω^2^ are used. These are sample-based or population-based estimators of explained variances, respectively. According to Cohen [56], η^2^/ω^2^ = .01 represents small, η^2^/ω^2^ = .06 represents medium, and η^2^/ω^2^ = .14 represents large effects.

Furthermore, identified relationships are tested for causality. This can be done by means of the study’s cross-lagged panel design (outcomes and confounding variables are collected at multiple measurement times). Here, linear structural equation modeling is used.

In order to clarify the mediating mechanisms as well as the modifiability of the identified associations, additional explorative path analyses are performed on mediating and moderating processes according to Hayes’ regression-based approach [57] using the SPSS®—macro “PROCESS” (current v. 3.4).

Moreover, data will be analyzed by multi-level modeling. Hereby, the repeated measures (level 1) will be nested in the patients (level 2). A simulation study shows that only small samples on level 2 (< *n* = 50) lead to biased estimations of the standard errors on level 2 [58]. Expecting invariant results, the exploratory application of these models can increase the assurance regarding the exclusion of small between subject effects.

In accordance with the ICH Guideline E9, the primary analyses are performed according to the intention-to-treat (ITT) principle. Per-protocol (PP) analyses on sensitivity of effects are implemented in an exploratory fashion.

In order to reliably estimate missing values and thus to protect the analyses against response and selection biases, multiple imputations will be used [59]. First of all, missing values will be tested by Little’s Missing-Completely-At-Random test [60]. Following a negative result, *n* = 20 data sets with all variables of the analytic model are estimated. Hereby, value estimations are restricted to scale-specific ranges. Results are then pooled over the *n* = 20 data sets.

In accordance with the methods proposed by the German Institute for Quality and Efficiency in Health Care (IQWiG), the cost-effectiveness analysis will be carried out from the perspective of the statutory health insurance and, if possible, additionally include a societal and/or individual perspective [61]. The incremental cost-effectiveness ratio (ICER) will be calculated dividing the difference in costs by the difference in health benefit of the intervention compared to standard care. Costs are assessed in monetary units, and the benefit is measured by the primary (severity of symptoms) and secondary outcomes (f. e. cesarean sections, health related quality of life). The perspective of the analysis thereby determines the relevant cost components.

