#### Objectives

This study aims to examine the clinical effectiveness and cost-effectiveness of an eMBI (*mindmom* app) within a sample of pregnant women during the third trimester of pregnancy who were screened positive for emotional distress.

The following content-related hypotheses will be examined:

Participation in the intervention leads to (a) decrease of symptoms of depression/anxiety or lowers prevalence of peripartum depression, (b) decrease of neuroendocrine stress markers, (c) increase of quality of life, (d) promotion of a more positive perception of the birth experience and attachment to the newborn, and (e) a reduction in the number of cesarean sections.

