## Intervention

### Electronic mindfulness-based intervention

The eMBI presented here (*mindmom intervention*) was adapted to pregnancy by an interdisciplinary team of gynecologists, psychologists, and midwives and takes place between the 29th and 36th gestational weeks [35]. The eMBI comprises an established concept of eight weekly 45-min sessions [34] including psychoeducational content, approaches derived from cognitive behavioral therapy and mindfulness exercises especially adapted to pregnancy [36]. *Mindmom* teaches how to deal with stress, pregnancy- and birth-related anxiety, and perinatal depressive symptoms and supports the autonomy of the expectant mother with regard to the upcoming birth and the initial time with the baby. The app contains instructional videos, audio files, interactive worksheets, and a personal skills box in which the participant can collect exercises, texts, and videos that were perceived as helpful. Table 1 gives an overview of the contents of the *mindmom* sessions.

**Table 1 Tab1:** Overview of the *mindmom* program

Module 1	Module 2	Module 3	Module 4	Module 5	Module 6	Module 7	Module 8
**Introduction** (the idea behind skill and mindfulness training)	**Fears and worries about birth/parenting**	**Coping with stress**	**Birth-related pain control**	**Birth**	**Me and my baby**	**Outlook puerperium**	**Graduation module—a review of all modules**

In order to improve adherence to the intervention, participants will be reminded by email about pending appointments and visits. Additionally, elements of gamification were implemented to support user compliance.

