**T6**	1st month postpartum	• Symptoms of depression and anxiety • Postpartum bonding • Satisfaction with medical care around the birth • Satisfaction birth • Breast feeding behavior • Blood pressure, weight • Medical details on current birth	EPDS, STAI PBQ-16 PEQ-G
**T7**	5th month postpartum	• Symptoms of depression and anxiety • Postpartum bonding • Mindfulness • Blood pressure, weight • Breastfeeding behavior • Morning cortisol profile • Technical handling and acceptance of the *mindmom* app	EPDS, STAI PBQ-16 FFA-14
**T1–7**	Continuously	• Out-of-pocket payments for alternative diagnostic and therapeutic methods, homeopathic products or non-prescription drugs	Cost diary

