#### Postpartum Bonding Questionnaire

The quality of postpartum bonding is evaluated by applying the abridged version of the Postpartum Bonding Questionnaire (PBQ-16) [47, 48]. The PBQ-16 consists of 16 items and has a good internal consistency (Cronbach’s α = .85).

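### The effect that Table 3 names for exploratory hypotheses 10–12, very probably postpartum bonding (PBQ-16), is a change between two post-treatment visits and would miss a benefit of equal size at both

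*Protocol article*

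**What the plan says.** - **Objective.** Under Objectives, hypothesis (d) expects the intervention to lead to "promotion of a more positive perception of the birth experience and attachment to the newborn".
- **Timing of treatment.** Under Electronic mindfulness-based intervention, the programme "takes place between the 29th and 36th gestational weeks".
- **Timing of bonding.** In Table 2, PBQ-16 appears at T6, 1 month postpartum ("Postpartum bonding • Satisfaction with medical care around the birth"), and at T7, 5 months postpartum ("Postpartum bonding • Mindfulness • Blood pressure, weight"), and at no other visit.
- **Test.** In Table 3, exploratory hypotheses 10–12 are a single test, "2 (group) × 2 (measurement)—ANOVA for repeated measures on the factor" measurement. The relevant effect for that row is "Group × measurement interaction effect".
- **Contrast within the same table.** The t-test row and the chi-square row name a group main effect instead.
- **Status.** The text below Table 3 tests exploratory hypotheses at an unadjusted .05 and treats their results as descriptive.

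**The concern.** A group × measurement interaction is a sensible treatment test when the first measurement precedes treatment. The groups then start level by randomization, and a treatment effect shows as divergence. This holds for the other repeated scales and for cortisol, all of which start at T1.

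It does not hold for an outcome seen only after treatment. With T6 and T7 alone, the interaction is the group difference at month 5 minus the group difference at month 1. That describes whether an effect fades or grows. Whether there is an effect is the group contrast, which randomization makes valid without a baseline.

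At stake is the reading of one secondary outcome. A stable benefit would leave the named effect non-significant, while a benefit that disappears would make it more likely to be significant. Because the exploratory results are meant to seed later research, the wrong hypothesis could be carried forward.

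**Working it through.** **1. Which outcome is in the row?** Table 3 names none, so this is an inference from counts in Table 2.

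| Outcome | Visits | Count | Matching row in Table 3 |
|---|---|---|---|
| MFAS | T1, T3, T5 | 3 | 2 × 3 ANOVA |
| EQ-5D | T1, T3, T5 | 3 | 2 × 3 ANOVA |
| FFA | T1, T5, T7 | 3 | 2 × 3 ANOVA |
| Morning cortisol | T1, T5, T7 | 3 | 2 × 3 ANOVA |
| PBQ-16 | T6, T7 | 2 | 2 × 2 ANOVA |
| PEQ-G | T6 | 1 | t test |

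Table 3 has four 2 × 3 tests, one 2 × 2 test and one t test, so the match is complete. Breastfeeding behaviour is also recorded at T6 and T7, but no scale is given and it is not a listed secondary outcome.

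**2. The plan's own figures.** Formulas are noncentral F, with correlation ρ = .5 and sphericity assumed because the article states neither.
- Interaction, 2 groups, m = 5, f = .10, α = .016: λ = f²·N·m/(1−ρ) = .01 × 196 × 5/.5 = 19.6, on 4 and 776 df. Power is .904. The smallest even N for .90 is 194, against 196 stated.
- Between-subject effect, N = 196, f = .10: power .269 (stated .27).
- Dropout: 196/.7 = 280. Exploratory error rate: 1 − .95⁹ = .370 (stated .37).
- Pilot effect: pooled SD = √[(20 × 5.22² + 28 × 4.94²)/48] = 5.06, and (6.62 − 4.90)/5.06 = .34, as stated.

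**3. The 2 × 2 row.** Let d₆ and d₇ be the standardized group differences at T6 and T7, with unit variances, correlation ρ between visits and N/2 per group. Both tests have 1 and N − 2 df, at α = .05.
- Interaction (difference scores, variance 2(1−ρ)): λ = (d₇ − d₆)²·(N/4)/[2(1−ρ)].
- Group main effect (mean of both visits, variance (1+ρ)/2): λ = [(d₆ + d₇)/2]²·(N/4)/[(1+ρ)/2].

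If d₆ = d₇, the first λ is 0 for any d and any ρ, so the rejection rate is α = .05.

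At N = 196, N/4 = 49. With ρ = .5:
- Equal benefit, d = .34: main effect λ = .1156 × 49/.75 = 7.55, power .78. Interaction λ = 0, rejection .05. A simulation of 20,000 trials gave .78 and .049.
- Halving to .17 at T7: interaction λ = .0289 × 49/1 = 1.42, power .22. Main effect λ = .0650 × 49/.75 = 4.25, power .54.
- Gone by T7: interaction λ = .1156 × 49/1 = 5.66, power .66. Main effect λ = .0289 × 49/.75 = 1.89, power .28.

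Range over ρ, N = 196 (interaction / main effect):

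| d₆, d₇ | ρ = .3 | ρ = .5 | ρ = .7 |
|---|---|---|---|
| .34, .34 | .05 / .84 | .05 / .78 | .05 / .73 |
| .20, .20 | .05 / .41 | .05 / .36 | .05 / .33 |
| .34, .17 | .17 / .60 | .22 / .54 | .33 / .49 |
| .34, 0 | .52 / .31 | .66 / .28 | .86 / .25 |

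**The case against.** - **The outcome is inferred.** Table 3 names none, and the numbered hypotheses are not in the article. This stands. The counts make PBQ-16 very probable, not certain.
- **Three hypotheses share one ANOVA.** One of hypotheses 10–12 could be a group contrast. This cannot be settled from the article. The row still lists one relevant effect, and it is the interaction.
- **Other parts of the plan look at group differences.** The same ANOVA yields the group main effect. The sample size section discusses power for between-subject effects. Dunn's procedure could compare the groups at each visit. The multi-level models are meant to help exclude small between-subject effects. All of this stands, so a reader who infers that the trial cannot detect a lasting bonding benefit, or would have to report none, goes beyond the documents. But none of these is named as the test for bonding, and relying on one after seeing the data would be an unplanned switch.
- **The row is exploratory.** This also stands. No primary conclusion and no part of the sample size depends on it.
- **The analysis plan may settle it.** That would answer an omission. Here the article fixes a specific effect, and it does not match the objective.

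**Conclusion.** The point holds as a should-fix. The effect named for hypotheses 10–12 does not address objective (d) for an outcome measured only after treatment.

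The firm result is that, under an equal benefit at T6 and T7, the named effect rejects at .05 regardless of effect size or correlation. This is specific to an equal benefit; one that changes between visits gives the interaction some power, and one that vanishes can give it more than the main effect.

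The main-effect figures are illustrative. The documents give no PBQ-16 effect size or between-visit correlation; d = .34 comes from EPDS in the pilot, and ρ was varied from .3 to .7. With d = .20, main-effect power is only .33 to .41, so naming the main effect removes the mismatch without ensuring adequate power.

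**What to change.** In Table 3, row 10–12, replace the interaction as the relevant effect by the group main effect (mean of T6 and T7), or by the group contrast at each visit. Keep the interaction as a description of whether any difference persists from month 1 to month 5. Name PBQ-16 in the row so that the link to objective (d) no longer has to be inferred.

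The cost is one table cell and an outcome label. No visit, questionnaire or participant is added, and the α level and number of exploratory tests stay the same if the main effect is chosen; contrasts at each visit would add one test to the count. The change should be recorded before bonding data are analysed by group.

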**Methods:**

Within the scope of the routine prenatal care, pregnant women attending routine pregnancy care in Baden-Wuerttemberg, Germany, are invited to participate in a screening for mental distress based on the Edinburgh Postnatal Depression Scale (EPDS). Women with an EPDS screening result > 9 will be referred to one of the *mindmom* coordinating study centers and are offered counseling either face-to-face or via videotelephony. After an initial psychological counseling, women are invited to participate in an eMBI in their last pregnancy trimester. The study will enroll *N* = 280 study participants (*N* = 140 per group), who are randomized 1:1 into the intervention (IG) or control group (treatment as usual = TAU).

All participants are requested to complete a total of 7 digital assessments (5 visits pre- and 2 follow-up visits postpartum), involving self-report questionnaires, sociodemographic and medical data, physiological measures, and morning cortisol profiles. The primary outcome will be depressive and anxiety symptoms, measured by the Edinburgh Postnatal Depression Scale, the State Trait Anxiety Questionnaire, and the Pregnancy-Related Anxiety Questionnaire. Secondary outcomes include mindfulness, satisfaction with birth, quality of life, fetal attachment, bonding, mode of delivery, and cost-effectiveness.

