## Background

Mental disorders, especially anxiety and depressive disorders, are common during the peripartum period and may have far-reaching consequences for both mother and child [1–3]. The prevalence of peripartum depressive disorders is reported to be approximately 9% in Germany [4]. With prevalence rates ranging between 39% ante- and 16.5% postnatally, most studies indicate that women are even more susceptible to anxiety disorders during pregnancy [2, 3]. Furthermore, anxiety and depression have a very high comorbidity of approximately 50% [5].

Maternal psychological distress has been linked to adverse peripartum health outcomes for both mother and child, such as preterm delivery, low birth weight, maternal substance abuse in pregnancy, impaired mother-child interaction, childhood regulatory dysfunction, and impaired cognitive and psychomotor development [3, 6, 7].

Furthermore, the rising rate of cesarean delivery, which is currently estimated at 31% in Germany, is known to be associated with maternal mental disorders [4]. About 80% of indications for cesarean section are relative indications, of which 10% are due to increased levels of maternal anxiety. Effective treatment of peripartum psychological distress could thus have the potential to lower the cesarean section rate [8].

As most antenatal care systems worldwide do not provide any structured screening for maternal mental health, mental illnesses are often overlooked and not treated adequately. Recent studies have shown that peripartum depression is not detected in 80% of women, and only 20% of those affected receive an appropriate treatment [9]. This appears even more relevant, as maternal mood disorders can lead to substantial health care and societal costs. Furthermore, the treatment of peripartum mental disorders is particularly challenging, as medical treatment is often rejected for fear of harming the fetus [10, 11]. Thus, there is a high demand for integrating a validated screening for maternal mental distress in routine antenatal care and for easily accessible non-medical treatment options during pregnancy.

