### Data analyses

The results will be reported following CONSORT recommendations [29]. All statistical analyses are conducted by using IBM® SPSS® and AMOS® (current version 26.0.0). Sociodemographic and clinical data will be described by means of frequencies and percentages or means and standard deviations. Confirmatory and exploratory research hypotheses will be analyzed using multivariate analysis of variance with repeated measurements, correlation analysis, and chi-square tests (see Table 3).

**Table 3 Tab3:** Analytic procedure

	Statistical test	Number of tests	Test statistic	Relevant effect

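### Table 3 names a two-cell goodness-of-fit χ² test for the exploratory categorical outcomes, where comparing proportions between arms needs the 2 × 2 table

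*Protocol article*

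**What the plan says.** The Data analyses section announces "multivariate analysis of variance with repeated measurements, correlation analysis, and chi-square tests (see Table 3"), and so refers the reader to Table 3 for the form of each test. Under the exploratory hypotheses, the row numbered 14 reads "One-dimensional *χ*^2^ test with 2 cells", with three tests and a group main effect as the relevant effect. No other row handles a categorical outcome, and no 2 × 2 or contingency-table test is named anywhere.

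The Objectives include, as hypothesis (e), "a reduction in the number of cesarean sections", and the Abstract lists among the secondary outcomes "fetal attachment, bonding, mode of delivery, and cost-effectiveness". The Background gives a cesarean rate "which is currently estimated at 31% in Germany".

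For the exploratory analyses, "the critical, local α-errors are not adjusted and set to a conventional level of α_local_ = .05". The text acknowledges "inflation of the global α-error by multiple testing (9 tests") to a global level of 0.37 and calls these analyses descriptive and hypothesis-generating.

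**The concern.** A χ² test with one dimension and two cells is a goodness-of-fit test. With group as the effect, the two cells can only be the number of events in the eMBI arm and the number in the TAU arm, set against an expected split. Women without the event do not enter. Comparing a proportion between two arms needs two dimensions and four cells: arm by event yes/no.

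Two things follow. First, the variance is wrong: the test treats the counts as if events were rare, so it is too conservative when they are common. Second, if the expected split is 50:50, as is usual for this test, a difference in the number of evaluable women can pass for a difference in risk. At stake is the error rate of the only significance tests planned for the binary outcomes, apparently including cesarean section.

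**Working it through.** **Inputs.**
- Allocation 1:1, 280 randomized (140 per arm), 30% dropout leaving 196 (98 per arm if dropout is equal): Randomization and Sample size.
- Local α = .05 for exploratory tests: Data analyses.
- Event rate 31%: the general German cesarean rate from the Background, assumed here for both arms under the null.
- Unequal splits and the alternative rates (18%, 20%) are assumptions; the article gives none.

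**The article's own figure.** The exploratory tests number 4 + 1 + 1 + 3 = 9, and 1 − (1 − .05)^9 = .370, which reproduces the stated 0.37. Three of the nine are these χ² tests, so the figure presumes that each has size .05. No power or sample size is stated for them.

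**Relation between the two tests.** Let a and b be the event counts, n the size of each arm, and p the pooled rate (a + b)/2n.
- Two-cell statistic: (a − b)²/(a + b).
- 2 × 2 Pearson statistic with equal arms: (a − b)²/[(a + b)(1 − p)].
- Hence two-cell = 2 × 2 × (1 − p).

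At p = .31 the two-cell test rejects only when the proper z exceeds 1.96/√.69 = 2.36. The large-sample two-sided size is therefore 2Φ(−2.36) = .018.

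**Size by exact binomial enumeration, 31% in both arms, nominal .05.**

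| Evaluable per arm | Two-cell, equal expected counts | Two-cell, expected counts weighted by arm size | 2 × 2 |
|---|---|---|---|
| 98/98 | .018 | .018 | .051 |
| 140/140 | .019 | .019 | .050 |
| 102/94 | .027 | .019 | .049 |
| 105/91 | .046 | .018 | .048 |
| 112/84 | .152 | .018 | .051 |
| 80/116 | .260 | .018 | .050 |

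The 105/91 split corresponds to 25% versus 35% dropout (105/140 = .75, 91/140 = .65), and 112/84 to 20% versus 40%.

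**Other event rates, equal arms.** Over assumed rates from 9% to 50%, the size of the two-cell test runs from about .04 down to .006.

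**Power (two-cell against 2 × 2).** 31% versus 18% at 140 per arm: .62 against .72. 31% versus 20% at 98 per arm: .31 against .43.

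**Worked example.** With 30/140 versus 45/140 cesareans:
- Two-cell: 15²/75 = 3.00, p = .083.
- 2 × 2: pooled rate 75/280 = .268, so 3.00/.732 = 4.10, p = .043.
- Two-cell on the women without cesarean, 110 versus 95: 15²/205 = 1.10, p = .295.

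So the two-cell answer also depends on which category is counted. The 2 × 2 answer does not.

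**The case against.** Several arguments limit the point, and most of them stand.

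- **The row is exploratory.** This is correct. The article calls these analyses descriptive and accepts a global error of 0.37. A reader might infer that the trial's main conclusions are at risk. They are not: neither the three confirmatory tests nor the sample size uses this row.
- **Cost-effectiveness.** Because cesarean section is named as a benefit measure, a reader might infer that the wrong test carries over into the economic result. It does not: the incremental ratio divides a difference in costs by a difference in benefit, and no p-value enters.
- **False positives.** A reader might take .15 as the expected error rate. It needs both equal expected counts and an assumed 20-point difference in dropout. The article gives only 30% overall. At a 10-point difference the size is .046, still within nominal, and with equal arms the test is conservative. If the planned multiple imputation covers these outcomes, the arms stay near 140 each.
- **Denominators.** It is tempting to say that the test necessarily ignores the number of women per arm. It need not, since expected counts can be weighted by arm size and the article does not say which are used. Weighting removes the imbalance bias but not the conservatism.
- **Link to cesarean section.** This is inferred. The numbered hypotheses are not printed, and 14 also falls within an ANOVA row (14–16). The inference rests on this being the only categorical row. The defect applies to any binary outcome tested this way.
- **Little power either way.** The Background attributes 10% of the 80% relative indications to anxiety: .31 × .80 × .10 = about 2.5 percentage points in the general population. For 31% versus 28.5% at 140 per arm, power is about .03 (two-cell) and .07 (2 × 2). Correcting the test would not make an effect of that size detectable.
- **A slip of terminology, or detail left to the analysis plan.** The authors may have meant the ordinary 2 × 2 test. If so, the row misnames it and needs the same edit. The article does not leave the choice open, because it specifies both the dimension and the number of cells.

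**Conclusion.** The concern holds as a moderate correction to one exploratory table row. The named test is not a two-arm comparison of proportions, and neither choice of expected counts makes it one. With equal arms at 31%, it runs at a size of .018 to .019 instead of .05 and gives up about 10 points of power in the 31% versus 18% case. Its error rate exceeds nominal only with equal expected counts together with clearly unequal evaluable arms.

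The figures rest on the general-population cesarean rate applied to both arms, on assumed splits and alternatives, and on a literal reading of the row.

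**What to change.** Replace the row with a 2 × 2 χ² test (arm by event yes/no) or a logistic regression with arm as the factor. Report the risk difference with its 95% CI for each of the three outcomes, and name those outcomes in the row so that the duplicate number 14 is resolved.

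State how missing event status is handled, consistently with the multiple imputation set out in Data analyses. Limiting the analysis to women with known status, without comment, would not fit that plan.

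The cost is one table row and a sentence. No additional data are needed, and neither the sample size nor the confirmatory analyses change.

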### Sample size

Estimation of sample size and power analysis were calculated with G*Power (Version 3.1.9.2) [32, 33]. The estimation was implemented for the confirmatory hypotheses, which aim for interaction between the between- (group) and within-subject factor (time of measurement), i.e., that the symptom burden develops differently in the two study groups over the course of time. The analysis with the lowest power is the two-factorial ANOVA with the outcome “PRAQ” (5 measurements, see Table 3, hypotheses 4–6).

The estimation is based on type 1 error of α = .016, Bonferroni-adjusted for 3 confirmatory analyses, and a power of 1 − β = .90. The statistically significant effect size is based on the results of a pilot study on mindfulness-based prevention in pregnant women with a history of depression [34]. Based on the mean values, standard deviations, and case numbers reported in this study, a final treatment effect of Cohen’s *d* = .34 (intervention group: *M* = 4.90, *SD* = 5.22, *n* = 21; control group: *M* = 6.62, *SD* = 4.94, *n* = 29) is calculated for the outcome “depressive symptoms” (EDPS score). According to Cohen (1988), this can be classified as a small effect size. Thus, the number of cases for the ANOVA design is estimated for small treatment effects (*f* = .10). Thus, *N* = 196 cases are needed to evaluate the eMBI. Assuming a dropout rate of 30%, the number of cases was determined to be *N* = 280 to reach a case number of *N* = 196 (*n* = 140 for each group or per region and *n* = 70 per group and region). With a sample size of *N* = 196, large- (*f* = .40) and medium-sized (*f* = .25) effects can be detected with a power of 1 − β = .99 and .98, respectively. Only small effects (*f* = .10) cannot be ruled out sufficiently with a power of 1 − β = .27 in case of non-significant between-subject effects.

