**Confirmative hypotheses**				
**1–3**	2 (group) × 7 (measurement)—ANOVA for repeated measures on the factor “measurement”	2	*F*-distribution	Group × measurement interaction effect
**4–6**	2 (group) × 5 (measurement)—ANOVA for repeated measures on the factor “measurement”	1	*F*-distribution	Group × measurement interaction effect

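### Optional improvement: Holm's step-down test in place of plain Bonferroni would add power for the second and third confirmatory outcomes at the same global α

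*Protocol article*

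**What the plan says.** Table 3 of the protocol article lists three confirmatory tests, each of a group × measurement interaction. Two are of the form "2 (group) × 7 (measurement)—ANOVA for repeated measures on the factor “measurement" and one has five measurements. The visit schedule in Table 2 matches this: EPDS and STAI are taken at all seven visits, PRAQ-R only at the five antenatal ones.

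The text below Table 3 sets the error control: "The critical, local α-errors for the 3 tests evaluating the confirmatory hypotheses are Bonferroni-adjusted to α_local_ = .05/3 = .016". The stated purpose is "to avoid exceeding a global α-error of α_global_ = .05 by performing multiple tests". No step-down or other sequential rule is mentioned.

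The Sample size section uses the same level: "type 1 error of α = .016, Bonferroni-adjusted for 3 confirmatory analyses, and a power of 1 − β = .90". It names the weakest test ("The analysis with the lowest power is the two-factorial ANOVA with the outcome “PRAQ” (5 measurements" in each subject) and arrives at 196 evaluable women, or 280 after 30% dropout.

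The Data monitoring section adds K = 3 interim analyses, one per 94 recruited women, with an α adjustment after Lan and DeMets.

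**The concern.** Plain Bonferroni ignores what the other two tests show. Suppose the three p-values were .001, .004 and .03. Under the written rule the third outcome is negative. Holm compares .001 with .0167, .004 with .025 and .03 with .05, and declares all three positive at the same global α.

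The objectives treat depression and anxiety together in one hypothesis, so more than one outcome responding is a result the trial hopes for. In that case the written rule gives up power that the global α of .05 would allow. What is at stake is a missed second or third outcome. No conclusion reached under the written rule would be invalid.

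**Working it through.** **Inputs from the protocol.** Global α .05; three tests; local α .05/3, written .016; f = .10; N = 196 in two groups; m = 5 measurements for PRAQ and 7 for the other two.

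**Assumed, because the article does not state them.** Within-subject correlation ρ = .5, sphericity (ε = 1), and correlation R between outcomes of 0, .5 or .7.

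**1. Reproducing the plan's figure.** For the within-between interaction with k = 2 groups, λ = f²·N·m/(1 − ρ), df1 = (k − 1)(m − 1), df2 = (N − k)(m − 1).

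- PRAQ: λ = .01 × 196 × 5/.5 = 19.6; df 4 and 194 × 4 = 776. Power at .016 is .904. The smallest N for .90 is 194, against 196 stated.
- Seven-measurement tests: λ = .01 × 196 × 7/.5 = 27.44; df 6 and 194 × 6 = 1164. Power at .016 is .966.
- 196/(1 − .30) = 280, as stated.

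The sizing is sound for the Bonferroni level under these assumptions.

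**2. Truncation.** .05/3 = .01667 and 3 × .016 = .048. PRAQ power is .904 at .016 and .906 at .01667, and N is 194 either way. This is negligible.

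**3. Bracket for Holm.** An outcome tested by Holm faces a threshold between .05/3 and .05. Its power therefore lies between the powers at those two levels: for PRAQ, between .906 and .959.

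**4. Simulation.** 200,000 runs, two seven-measurement tests and one five-measurement test, chi-square approximation to the interaction F, N = 196, ρ = .5. Bonferroni is taken at the exact .05/3.

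All three effects real, f = .10:

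| R | PRAQ, Bonferroni → Holm | All three, Bonferroni → Holm | At least one, both rules |
|---|---|---|---|
| 0 | .908 → .959 | .851 → .937 | .9999 |
| .5 | .908 → .956 | .871 → .942 | .997 |
| .7 | .910 → .955 | .885 → .947 | .992 |

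Each seven-measurement outcome goes from about .97 to .98–.99.

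Only PRAQ responds (R = .5): .908 → .909.

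Smaller effects, f = .07 on all three (R = .5): PRAQ .536 → .634; all three .348 → .518; at least one .859 under both.

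**5. Family-wise error (R from 0 to .7).** Global null: .043 to .050, the same for both rules. Two true effects and one null: about .016 for Bonferroni and .048 for Holm, both within .05.

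**6. If ρ is lower.** At ρ = .3, PRAQ power at N = 196 is .744 at .016. The bracket of step 3 becomes .749 to .864, so there is more to gain.

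**7. Interim looks.** Suppose three equally spaced looks test efficacy, with the third as the final one, at α = .05/3 for a one-degree-of-freedom test. This is illustrative, since the article gives neither the spending function nor the information fractions. Pocock-type spending α·ln(1 + (e − 1)t) has used .01667 × ln(1 + 1.718 × 2/3) = .0127 by t = 2/3, which leaves .0039. The Lan-DeMets nominal level at the final look is .0064. With O'Brien-Fleming-type spending the two figures are .0142 and .0159. The unspent α is the smaller figure in both cases. Using it as Holm's first threshold would be stricter than the group-sequential boundary already implied by the plan.

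**The case against.** The strongest reply is that nothing here is wrong. Bonferroni holds the global α, is applied in the same way in the sample size and the analysis, and the sizing reproduces. That stands, and it makes this an optional gain, not a defect. The rule is, however, fixed outright in the protocol, so it is fair to comment on it without the analysis plan.

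Four stronger readings may tempt a reader.

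- *Holm is more powerful throughout.* It is not. Its first step is Bonferroni's, so the chance of at least one rejection is identical, and if only PRAQ responds the gain is about .001. Nor do the documents require all three outcomes for success, so the all-three figure describes how complete the result is, not whether the trial succeeds.
- *The outcomes are correlated, and that is where Holm gains most.* The reverse holds. The all-three gain falls from .086 (.937 − .851) at R = 0 to .062 (.947 − .885) at R = .7. What produces the gain is that all the effects are real.
- *The sample size could be cut.* It could not on this ground, because the first Holm step is still at .05/3.
- *The change costs nothing.* Simple simultaneous intervals that agree with the decisions are lost, and the step-down levels must be coordinated with any efficacy looks.

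**Conclusion.** This is a cheap, optional improvement to a valid rule. Holm keeps the protocol's own guarantee of .05, loses no rejection that Bonferroni would make at a single final analysis, and helps when two or three outcomes respond. At the design point PRAQ power rises by about 5 points (.91 to .956) and the chance that all three are significant by about 7 points (.87 to .94).

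These sizes rest on f = .10 for every outcome, N = 196, within-subject correlation .5, sphericity and a between-outcome correlation of .5. Varying the last from 0 to .7 moves the Holm figures little: PRAQ .955 to .959, all three .94 to .95. The gains are larger if actual power is below plan, as with f = .07 or a lower within-subject correlation. They are near zero if a single outcome responds.

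The documents do not support calling the Bonferroni rule an error, the .016 a material loss, or the sample size wrong on this account.

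**What to change.** Replace the Bonferroni sentence in Data analyses by: *The three confirmatory p-values are tested by Holm's procedure (.05/3, .05/2, .05) at a global α of .05.* Leave the sample size at .05/3, which is the first Holm step. Make the change before any unblinded result is seen.

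State whether the looks in Data monitoring test efficacy. If they do, add that the final-analysis threshold at each Holm step is the Lan-DeMets boundary computed for that step's α (.05/3, .05/2 or .05), not the α left unspent.

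Cost: one sentence, plus one clause and a set of boundary calculations if there are efficacy looks. N, data collection and the tests themselves do not change. The price is less simple simultaneous confidence intervals. A sponsor who values those more may reasonably keep Bonferroni.
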